#### Data analyses

Patients will be included in intent-to-treat analyses. Participants’ demographic characteristics will be summarised using descriptive statistics, and the comparability of the treatment groups will be examined using *χ*^2^ tests for categorical variables and *t* tests for continuous variables.

Data analyses of the primary and secondary outcomes will be conducted using generalised estimating equation (GEE) models. Essentially, GEE models extend generalised linear models (GLMs) to allow analysis of repeated measurements or other correlated observations. The response can be scale, counts, binary or events-in-trials. In addition, GEE models can also deal with data that have missing values as long as the missing value is completely random. Parameter estimation can still yield robust results [51].

In these GEE models, treatment conditions (experimental vs. control) will be included as the between-subjects factor and time (baseline, after treatment and at 12 month follow-up) as the repeated measure. Main effects and interaction between treatment and time will be examined. When the interaction effect is statistically significant, simple main effects analyses will be conducted.

IBM SPSS (version 22.0 for Windows) will be used for the statistical data analyses. Statistical significance will be defined as *p* < .05. Bonferroni correction will be applied for post hoc multiple comparisons.

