#### Sample size

The sample size calculation is based on our primary outcome measure, BPD symptom severity at 12 months. A sample size of 26 participants per group is required to detect a post-treatment effect size of 0.20 (Cohen’s d) between both groups with a power of 0.80 in a one-tailed test and with a 95% confidence level. This corresponds to the estimated differences between groups of about 8.6 BSL-23 raw scores. Therefore, the total sample size is determined at 52 participants. Dropout rates for BPD patients are 24% to 52% [50]; therefore, we need to recruit at least 72 individuals.

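### GEE is a large-sample method used here with 26 to 36 patients per arm; if its robust Wald test is left uncorrected, the nominal 5% interaction test rejects about 6 to 7% of the time

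*Protocol article*

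**What the plan says.** The Data analyses section of the protocol article assigns one method to all outcomes: "Data analyses of the primary and secondary outcomes will be conducted using generalised estimating equation (GEE) models". The model has treatment arm, three time points and their product: "Main effects and interaction between treatment and time will be examined". A further step depends on the interaction: "When the interaction effect is statistically significant, simple main effects analyses will be conducted". The threshold is given as "Statistical significance will be defined as *p* < .05", the population as "Patients will be included in intent-to-treat analyses", and the software as "IBM SPSS (version 22.0 for Windows) will be used for the statistical data analyses". The section accepts GEE with missing values on condition that they are missing completely at random.

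On numbers, the Sample size section says "A sample size of 26 participants per group is required" and recruits 72, allocated 1:1. Expected dropout is 24 to 52% in that section and 24 to 58% in the limitations paragraph of the Discussion.

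The article does not say which variance estimator the GEE uses, which reference distribution its tests use, or whether a small-sample correction applies.

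**The concern.** GEE inference is justified as the number of independent subjects grows. Two approximations can fail with a few dozen patients per arm. First, the usual robust variance is built from residuals around fitted means and is biased downward. Second, a chi-square or normal reference treats that variance as known. Both push toward rejecting too often. This happens even with complete, normally distributed data and no correlation between patients treated in the same therapy group.

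The treatment-by-time test matters most because it opens the way to the simple main effects, including the between-arm comparison at post-treatment that the Study aims section names as the primary outcome. If its actual error rate exceeds 5%, the confirmatory claim is somewhat weaker than stated. For a continuous score at these sizes, a method with finite-sample degrees of freedom is available.

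**Working it through.** **Inputs from the article**
- Randomised per arm: 72 / 2 = 36.
- Planned evaluable per arm: 26, taken as stated. Whether 26 follows from the stated effect size is a separate question.
- Completers per arm at the upper dropout figures: 36 × (1 − 0.52) = 17.3 and 36 × (1 − 0.58) = 15.1, taken as 17 and 15.
- Nominal level: 0.05. The article gives no other error rate to reproduce.

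**Assumptions**
- Identity link, saturated arm-by-time means, normal data, patients independent.
- Two-sided tests, because the analysis section does not state sidedness.
- Uncorrected sandwich variance with a Wald chi-square test. This is an assumption about what will be run, not something the article says.
- Within-patient correlation is not given for the trial. Values of 0.5 and 0.73 (the test-retest figure quoted for the BSL-23) were both simulated.

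**Complete data.** With n per arm, the sandwich divides each arm's sum of squares by n where n − 1 is unbiased. The standard error therefore shrinks by √((n − 1)/n).
- Single baseline-to-post-treatment contrast (1 df): size = P(|t| > 1.96 × √((n − 1)/n)) with 2n − 2 degrees of freedom.
- Treatment-by-time (2 df): the statistic is a rescaled Hotelling T², and its tail reduces to size = (1 + 5.9915/(2n))^(−(2n − 3)/2). For n = 36 this is (1.0832)^(−34.5) = 6.34%.

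| n per arm | SE factor | 1 df, formula | 1 df, simulated | 2 df, formula | 2 df, simulated |
|---|---|---|---|---|---|
| 36 | 0.986 | 5.7% | 5.7% | 6.3% | 6.3% |
| 26 | 0.981 | 6.0% | 5.9–6.1% | 6.9% | 6.9% |
| 17 | 0.970 | 6.6% | 6.6% | 8.1% | 7.9–8.1% |
| 15 | 0.966 | 6.9% | 6.8–6.9% | 8.6% | 8.5–8.6% |

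The simulations used 200,000 null trials per setting; the ranges cover the two correlations. A one-sided 1-df test at 5% has a size of 5.5% (n = 36) to 6.2% (n = 15).

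**All 72 patients kept, dropout completely at random.** Exchangeable working correlation, data correlation 0.5, 4,000 trials per setting, Monte Carlo standard error about 0.4 points:

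| Dropout at both follow-ups | 1 df | 2 df |
|---|---|---|
| 0% | 6.2% | 6.3% |
| 24% | 6.5% | 6.5% |
| 52% | 6.6% | 7.7% |
| 58% | 7.2% | 8.9% |

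The mean estimated standard error is about 96 to 97% of the empirical one.

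**Model-based variance instead.** With a correctly specified exchangeable structure and a chi-square reference, the 2-df size is the F(2, v) tail at 5.9915/2 with v = 4(n − 1), which equals (1 + 5.9915/v)^(−v/2). At n = 36, v = 140 and the size is 5.3%. At n = 26, v = 100 and it is 5.45%. At n = 15, v = 56 and it is 5.8%.

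**After correction.** Scaling the robust variance by n/(n − 1) and using a t or F reference gives 4.9 to 5.05% (1 df) and 4.85 to 5.04% (2 df) at every n from 15 to 36.

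**The case against.** The strongest reply is that the article never commits to the uncorrected test. It names GEE and the software, and the sentence is compatible with a corrected variance and an F reference, which the working shows to be correctly sized. Details of this kind are commonly left to a full protocol or SAP that is not shown. This stands: a reader might infer that the standard errors are too small and the test invalid, but the article does not support that as fact. Its silence on the estimator is not itself the fault. What remains is that GEE was chosen for a continuous outcome at a size where its default inference needs correction.

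The effect is also modest at planned numbers: 1 to 2 points for the interaction and about 1 for the single contrast. That stands too. Fifteen per arm is a worst-case completer count, not the number in an intent-to-treat GEE, where patients with only a baseline value still contribute. Keeping all 72 does not remove the inflation, however, as the dropout simulation shows.

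Two further readings go too far. A reader might take the interaction to decide whether any between-arm comparison is made, but main effects are examined regardless and only the simple main effects are conditional. A reader might also take the section's remark on robust results as a reference to the robust variance; it concerns estimation with missing values.

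Finally, replacing GEE may look like preference, since a correction within GEE restores the level. That is fair on type I error alone. The mixed model has the additional advantage of a weaker missing-data assumption.

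**Conclusion.** The point holds conditionally and is modest in size. If the uncorrected sandwich Wald chi-square test is used, the nominal 5% interaction test has a type I error of about 6.3 to 6.9% at 36 to 26 per arm and about 8 to 9% only at 52 to 58% dropout. For the single contrast the figures are about 5.7 to 6.1%, rising to about 7%. Under a model-based variance with a chi-square reference, the interaction test is at about 5.3 to 5.8%.

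These figures rest on normal data, independent patients and, where dropout is simulated, completely random missingness. Clustering within therapy groups was not modelled. The plan should be improved here because the remedy is cheap, but the planned analysis has not been shown to be invalid.

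**What to change.** For BSL-23 and the other continuous outcomes, replace the GEE with a linear mixed model for repeated measures: the same fixed effects (treatment, time, interaction), unstructured covariance, REML, and Satterthwaite or Kenward-Roger degrees of freedom, whichever the chosen software provides. Being likelihood-based, it needs missingness at random rather than completely at random, which matters with 24 to 58% dropout expected.

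If GEE is kept, and for binary or count outcomes in any case, state a bias-corrected covariance and a t or F reference.

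This changes the analysis wording and needs no new data. Intervals become slightly wider and p values slightly larger.

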
Notes. ^a^All patients are free to contact the principal investigator throughout the process to solve practical questions about the use of session contents. ^b^10–12 group sessions given by 2 specifically trained psychologists using the guideline draft. ^c^11 group sessions given by 2 psychologists using a non-manualized program

A total of 3 more group sessions (2 of them matched with the assessment) will be delivered by the therapist and co-therapist after treatment and at 6 and at 12 months follow-up as well as an undetermined number of face-to-face sessions with the principal investigator. The same is true for the Structured Support Therapy group. These sessions are aimed to assure participants’ needs are met and to minimise dropout rates in both groups. Nevertheless, the Iconic Therapy group will continue to see and reinforce visual images, whereas those in the control group will receive plain verbal explanations without illustrations.

As this is the first time the Iconic Therapy programme is being delivered by therapists other than its creator or principal investigator, group sessions will be supervised from behind a unidirectional window by the principal investigator. Also, two Iconic Therapy randomised group sessions will be recorded by the creator for analysis. During the 10–12 week period of the study, supervision and feedback will be given to the therapist and co-therapist of both study groups.

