Specific therapies of this type may help sustain BPD sub-threshold symptoms and decrease health service and non-health care related costs derived from BPD diagnosis. Validating a treatment that has been showing good clinical results on severe BPD symptoms is not only an encouraging point of departure but also a priority. In this study, we test Iconic Therapy against Structured Support Therapy. We did not compare Iconic Therapy with any specialised treatment for BPD (i.e., DBT, TFT or MBT), as our objective was to empirically support that Iconic Therapy is more effective in reducing BPD symptoms than non-specialised treatment.

Finally, a number of potential limitations should be indicated. First, the sample size is small, and this may alienate results from its generalisation. Second, the age range for recruitment is limited (15 to 25 years old); therefore, the recruitment flow may be delayed. Third, heterogeneity on suicidal ideation severity and self-injuring behaviour frequency/lethality may affect treatment adherence, although symptom severity does not seemingly affect adherence to prescriptive therapies [59]. Fourth, the expected rate of dropouts for BPD is high (24% to 58%), and a high dropout rate may slant results [50]. Fifth, the 30 min shorter duration of the Structured Support Therapy group might interfere with the placebo control effect. Sixth, we used self-report questionnaires and not structured clinical interviews, which could represent a limitation despite the adequate psychometric properties of the instruments used.

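### The primary GEE is justified only for completely random missingness, which conflicts with the dropout the protocol itself expects

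*Protocol article*

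**What the plan says.** Four parts of the protocol article bear on this.

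- **Method and its condition (Data analyses).** "Data analyses of the primary and secondary outcomes will be conducted using generalised estimating equation (GEE) models". On missing data the section says that "GEE models can also deal with data that have missing values as long as the missing value is completely random". The analysis population is set by "Patients will be included in intent-to-treat analyses". No other approach to missing data is given.
- **Expected dropout.** Sample size: "Dropout rates for BPD patients are 24% to 52% [50]; therefore, we need to recruit at least 72 individuals". Discussion, limitations: "the expected rate of dropouts for BPD is high (24% to 58%), and a high dropout rate may slant results". Both cite the same reference but give different upper limits.
- **What may drive dropout.** The Discussion says that "heterogeneity on suicidal ideation severity and self-injuring behaviour frequency/lethality may affect treatment adherence", then adds that symptom severity does not seem to affect adherence to prescriptive therapies. The Structured support therapy group section keeps that arm's sessions at 60 minutes, partly because longer ones might harm adherence. Iconic Therapy sessions last 90 minutes.
- **Where outcomes are measured.** Table 2 puts the post-treatment evaluation in session 11 and the 12-month evaluation in session 13, in both arms. The text after the table begins "A total of 3 more group sessions (2 of them matched with the assessment".

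**The concern.** Completely random loss costs precision but does not bias a comparison. A protocol that says its dropout "a high dropout rate may slant results" therefore does not expect loss of that kind, yet completely random loss is the only condition under which it defends its primary analysis. This is a conflict between two stated positions, not detail left to a fuller document.

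The other passages make the conflict more than verbal. Severity and session length are both named as possible influences on adherence, and session length differs by arm. Because the outcome visits coincide with therapy sessions, a participant who stops attending may also be lost to measurement. If the reasons for stopping are related to severity and differ between arms, the treatment contrast can be biased in either direction.

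**Working it through.** **1. The plan's own dropout figures.** 52 completers out of 72 recruited means a loss of 1 − 52/72 = 27.8%, near the low end of either quoted range. If dropouts have no follow-up data, the expected number with outcomes is:

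| Dropout | 72 × (1 − dropout) |
|---|---|
| 24% | 54.7 |
| 52% | 34.6 |
| 58% | 30.2 |

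The amount of missing data could therefore be large.

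**2. Size of the possible bias.** The article gives no dropout model, so these inputs are assumptions:

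- BSL-23 standardised to SD 1, normally distributed, with no true effect;
- baseline–follow-up correlation r of 0.5, or of 0.73 (the test-retest value the protocol quotes for the Spanish BSL-23, used as a stand-in);
- dropout of 38% in each arm, the midpoint of 24% and 52%;
- log-odds of dropout rising by ln 2 per SD of baseline (odds ratio 2);
- independence working correlation, so the GEE contrast uses available-case means.

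Let δ be the mean baseline score of those who stay, relative to the whole arm. Integrating the logistic dropout curve over a standard normal baseline gives δ = −0.239 at 38% dropout. The follow-up mean of those who stay shifts by r × δ, while the baseline mean still uses everyone. The bias in an arm's change is therefore r × δ, and the bias in the contrast is the difference between arms.

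| Dropout depends on baseline | r = 0.5 | r = 0.73 |
|---|---|---|
| in one arm only | 0.5 × 0.239 = 0.12 SD | 0.73 × 0.239 = 0.17 SD |
| in opposite directions by arm | 2 × 0.12 = 0.24 SD | 2 × 0.174 = 0.35 SD |
| equally in both arms | 0 | 0 |

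At 24% dropout δ = −0.153, giving 0.08 to 0.11 SD (one arm) and 0.15 to 0.22 SD (opposite directions). At 58% δ = −0.363, giving 0.18 to 0.27 SD and 0.36 to 0.53 SD.

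**3. The same scenario with a correct working correlation.** Solving the GEE with the working correlation set to the true r gives a bias of 0.00 in every cell. A likelihood-based model also gives about zero when dropout depends only on observed baseline.

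**4. Dropout that depends on the unseen outcome.** With r = 0.6, log-odds of 1 per SD of the post-treatment score, and dependence in one arm only, both methods are biased. At 24%, 52% and 58% dropout the available-case contrast is off by 0.20, 0.43 and 0.48 SD, and the likelihood-type estimate by 0.13, 0.29 and 0.32 SD. A mixed model reduces this problem but does not remove it, hence the sensitivity analysis.

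**5. Small-sample test size (secondary).** With no true effect, the robust 2-df Wald test of the interaction rejects 6.2% of the time at 36 per arm with complete data. It rejects 6.6% to 7.1% with 36 per arm and 24% to 52% completely random dropout. The nominal level is 5%.

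**The case against.** The strongest reply is that the bias in step 2 is not a property of the plan as stated. The article does not name a working correlation, which an article may leave to the full protocol, and step 3 shows that a correct one removes the bias in this scenario. Bias also needs dropout to depend on severity differently by arm. Nothing in the article says it will, and the Discussion's remark about prescriptive therapies points the other way. All of this stands: the figures show what could happen, not what is expected. The reply does not touch the stated justification, which remains completely random missingness.

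Three stronger readings are tempting, and the documents do not support them.

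- **That intention-to-treat cannot be honoured.** Evaluations are scheduled with sessions 11 and 13, but the article sets no attendance condition for assessment. It defines treatment completion (at least 8 group sessions) separately, and it describes travel support, reminders and individual sessions to limit dropout.
- **That the bias can be given in BSL-23 points against the 8.6-point target.** The article states no SD. Its d of 0.20 with 8.6 points implies 8.6/0.20 = 43, while 26 per group at 80% one-sided power implies d of about 0.69 and so 8.6/0.69 = 12.5. Neither is a safe basis for conversion.
- **That p-values are seriously too small.** Treating 52% loss as 36 × 0.48 ≈ 17 per arm gives rejection rates of 8% to 9%, but GEE keeps the baselines of all 36. The realistic figure is 6% to 7%.

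**Conclusion.** The point holds in a limited form. The condition on which the protocol rests its primary analysis is inconsistent with the dropout it expects and with the influences on adherence it names. That is a reason to change the text now, because outcomes not collected from people who leave therapy cannot be recovered later.

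The possible bias in the treatment contrast is roughly 0.1 to 0.35 SD at 38% dropout. This rests on an available-case or independence-working-correlation analysis, an odds ratio of 2 per SD of baseline, r between 0.5 and 0.73, and dependence that differs by arm. That missing outcomes will follow therapy dropout is a reasonable inference from the schedule, not something the article says. The modest inflation of the robust test is a minor additional reason. This is a recommended improvement, not a fatal flaw.

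**What to change.** - **Data analyses.** Replace the completely-random justification. Make the primary analysis of BSL-23 a likelihood-based mixed model for repeated measures (SPSS MIXED) with all three time points, including baseline, and treatment, time and their interaction. State that it assumes data missing at random. Keep GEE as a sensitivity analysis, and add one sensitivity analysis for data missing not at random.
- **Data collection.** State that the BSL-23 is sought from every randomised participant after treatment and at 12 months, whether or not they attend the sessions. As a self-report form it can be completed by post, telephone or online.
- **Dropout range.** Reconcile 24% to 52% (Sample size) with 24% to 58% (Discussion).

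The cost is slightly more analysis work in the software already planned, and a small effort to reach non-attenders. Neither the design nor the number randomised needs to change for this point.

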### Study aims

The aim of the study is to investigate, by comparison with Structured Support Therapy, how effective Iconic Therapy is in improving participants’ BPD symptoms. The primary outcome measure is a change of symptoms measured through the use of the Borderline Symptom List (BSL-23) post-treatment. Our hypothesis is that patients undergoing Iconic Therapy will show a greater reduction in the severity of their symptoms after receiving the intensive part of the therapy than those undergoing Structured Support Therapy. As a secondary outcome, we hypothesise that these differences will continue to be verifiable at the 12-month follow-up. Other secondary measures are suicidal ideation, suicidal behaviour, maladjustment to daily life and use of services as a consequence of BPD symptoms. We will also evaluate satisfaction with the treatment and perceived subjective global improvement beyond the symptoms.

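### The stated power of 0.80 belongs to a one-tailed two-group comparison, not to the planned analysis, which reaches the primary post-treatment contrast only through a 2-df interaction gate

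*Protocol article*

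**What the plan says.** - **Study aims:** "The primary outcome measure is a change of symptoms measured through the use of the Borderline Symptom List (BSL-23) post-treatment". A lasting difference at 12 months is a secondary hypothesis.
- **Sample size:** the calculation is attached to symptom severity at 12 months, yet is meant to "detect a post-treatment effect size of 0.20" (Cohen's d) "with a power of 0.80 in a one-tailed test and with a 95% confidence level". It gives: "A sample size of 26 participants per group is required", so "the total sample size is determined at 52 participants". The effect is equated with "estimated differences between groups of about 8.6 BSL-23 raw scores". Recruitment is raised to 72 for dropout.
- **Data analyses:** primary and secondary outcomes go into a GEE with treatment, time (three levels) and their interaction. "When the interaction effect is statistically significant, simple main effects analyses will be conducted". Significance is p < .05, with no sidedness given. "Bonferroni correction will be applied for post hoc multiple comparisons"; the family of comparisons is not named.

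**The concern.** The primary question in the study aims is one directional contrast: do the arms differ in BSL-23 change by the end of treatment? The sample size section powers a single one-tailed comparison. The data analyses section contains no such test. Two arms by three times give an interaction on (2 − 1) × (3 − 1) = 2 degrees of freedom, which has no direction and mixes the post-treatment and 12-month effects. The post-treatment difference is looked at only after that test succeeds.

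Two things are at stake. The advertised power does not describe the test that will decide the trial. And a real post-treatment benefit can be lost at the gate, while a significant interaction does not by itself show at which time the arms differ. The treatment main effect is no substitute, because it averages in baseline, where randomised arms cannot differ by treatment.

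**Working it through.** **1. The plan's own figure.** Inputs from the sample size section: n = 26 per arm, d = 0.20, one-tailed alpha 0.05. For a two-sample t-test the noncentrality is d√(n/2) = 0.20 × √13 = 0.20 × 3.606 = 0.72 on 50 df.
- Power is 0.18 one-tailed and 0.11 two-tailed. The stated 0.80 is not reproduced.
- Required n per arm for 0.80 at d = 0.20 is 2(1.645 + 0.842)²/0.20² = 309.1, so 310 one-tailed; 2(1.960 + 0.842)²/0.20² = 392.5, so 393 two-tailed.
- Solving backwards, 26 per arm gives 0.80 one-tailed at d ≈ 0.70 (noncentrality 0.70 × 3.606 = 2.52). The 8.6-point difference then implies an SD of 8.6/0.70 = 12.3, against 8.6/0.20 = 43 at the stated d. The article gives no SD.

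**2. Sidedness.** At d = 0.70 and 26 per arm, the two-tailed t-test has power 0.70. A gated procedure must pass the interaction and this comparison, so it can have no more power than the comparison alone: about 0.70, whatever the correlation.

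**3. The planned sequence.** Simulation, 20,000 trials per setting, complete data, 26 per arm, constant within-person correlation r. Assumptions, none stated in the article: post-treatment d = 0.70; 12-month d = 0.70, 0.35 or 0; r = 0.3, 0.5 or 0.73. The last is the BSL-23 test-retest figure, the only correlation over time that the article gives for this scale. The interaction is a 2-df Wald test with robust variance, followed by a two-sided post-treatment arm comparison. Ranges run over the three 12-month effects.

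| r | Interaction alone | Interaction and post-treatment, 0.05 | Same, 0.05/3 | Ungated, baseline-adjusted, 0.05 |
|---|---|---|---|---|
| 0.3 | 0.50–0.62 | 0.43–0.54 | 0.38–0.46 | 0.73 |
| 0.5 | 0.64–0.76 | 0.53–0.62 | 0.45–0.51 | 0.81 |
| 0.73 | 0.89–0.96 | 0.67–0.70 | 0.53–0.56 | 0.95 |

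Repeat runs move entries by about 0.01, so the overall ranges are about 0.49–0.96, 0.43–0.70, 0.37–0.55 and 0.73–0.95. A small-sample F test in place of the Wald test lowers the gated ranges to 0.38–0.68 and, at 0.05/3, 0.32–0.52.

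**4. Why adjustment helps.** Baseline adjustment divides the effective d by √(1 − r²): 0.70/0.954 = 0.73 at r = 0.3, 0.70/0.866 = 0.81 at r = 0.5 and 0.70/0.683 = 1.02 at r = 0.73. This matches the last column.

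**5. At the stated d = 0.20.** The gated comparison has power of at most about 0.04. The adjusted contrast has an effective d of 0.20/0.954 = 0.21 to 0.20/0.683 = 0.29, and power of about 0.11 to 0.18.

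**The case against.** - **The interaction may itself be the primary test.** The hypothesis is a greater reduction, which is a difference in change, and a group-by-time interaction tests that. Baseline is in the model as an outcome, so it is not ignored. This stands in part: at r = 0.73 and d = 0.70 the interaction alone has power of 0.89–0.96. It would be wrong to infer that a 2-df interaction necessarily means an underpowered trial. But at r = 0.3 to 0.5 it has 0.50–0.76, and the article does not say which test decides.
- **Bonferroni may not touch the primary contrast.** The text limits it to post hoc comparisons and names no family; it may concern pairs of times within an arm. This stands. A reader might infer power of about 0.4 to 0.55 for the primary hypothesis. That needs d = 0.70, a chosen correlation and a threefold Bonferroni on the primary contrast, none of which the article states.
- **The sizing may have been an interaction calculation.** A total of 52 is returned by a group-by-time interaction with f = 0.20, two measurements, correlation 0.5 and two-sided alpha 0.05 (power 0.807). This is only an inference: the article says Cohen's d and one-tailed, and the trial has three measurements.
- **More patients may be retained.** With all 72 followed (36 per arm), the gated comparison without Bonferroni reaches 0.54–0.83 at d = 0.70. But the article expects 24% to 52% dropout and bases its power on 52.
- **Detail may sit in an analysis plan.** Contrast specification can. The gate and the one-tailed sizing are both fixed in the article, however, and they do not match.

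**Conclusion.** The mismatch holds on the text alone: the test that was sized is not the test that is planned, and the primary post-treatment difference is conditional on a non-directional interaction. The stated 0.80 is therefore not the power of the planned analysis.

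The size of the loss cannot be read from the article, because it gives no SD, no design correlation, no separate 12-month effect and no Bonferroni family. Under the assumptions above, the gated comparison at 26 per arm stays below 0.80 in every setting tried and below the ungated adjusted contrast in every setting. A single narrow power figure is not supported.

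The effect size is a separate and larger error: with the stated d = 0.20, even the one-tailed comparison has power 0.18. Using d = 0.70 is generous to the plan. Correcting d would still leave the trial sized for a test it does not run.

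**What to change.** 1. Reconcile the primary time point: post-treatment in the study aims, 12 months in the sample size section.
2. Define the primary test as one prespecified arm contrast in BSL-23 at that time, adjusted for baseline BSL-23 (already collected), with sidedness and alpha stated, no interaction gate and no Bonferroni on it.
3. Make the other time point secondary, and keep Bonferroni for the remaining comparisons, with the family named.
4. Restate the power for that contrast with an explicit effect size, SD and baseline correlation. Make d and the 8.6-point difference agree.

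Items 1 to 3 cost only wording and no extra data. Item 4 may cost more. If d ≈ 0.70 was meant, the adjusted two-sided contrast reaches about 0.80 with 26 per arm once r is about 0.5 or higher, and 0.73 at r = 0.3. If d = 0.20 was meant, no rewording brings 52 participants near 0.80, and the sample size or the target effect must be reconsidered.

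### The primary post-treatment contrast is reached only through a significant treatment-by-time interaction, and on a natural reading under Bonferroni, while the sample size assumes one ungated, uncorrected one-tailed test

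*Protocol article*

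**What the plan says.** - **Protocol article, Study aims:** "The primary outcome measure is a change of symptoms measured through the use of the Borderline Symptom List (BSL-23) post-treatment". The same section makes persistence of the difference at the 12-month follow-up a secondary outcome.
- **Protocol article, Sample size:** the section opens differently, "The sample size calculation is based on our primary outcome measure, BPD symptom severity at 12 months", and then continues: "A sample size of 26 participants per group is required to detect a post-treatment effect size of 0.20" (Cohen's d), "with a power of 0.80 in a one-tailed test and with a 95% confidence level". It equates this effect with about 8.6 BSL-23 points and makes no allowance for multiplicity.
- **Protocol article, Data analyses:** GEE models with treatment, time (three visits) and their interaction. Then: "When the interaction effect is statistically significant, simple main effects analyses will be conducted". The significance level is .05 with no sidedness given. The section closes with: "Bonferroni correction will be applied for post hoc multiple comparisons". The comparisons in that family are neither listed nor counted.

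**The concern.** With two arms and three visits, the interaction has 2 degrees of freedom. Neither it nor the main effects isolate the post-treatment difference. The only step described that does so is the simple effect, which is run only if the interaction is significant. Simple effects are also the only follow-up comparisons described, so the Bonferroni sentence naturally attaches to them.

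One pre-specified contrast needs neither a gate nor a correction. Requiring the interaction first means that a real post-treatment difference can go undeclared because the 2-df test missed. If Bonferroni applies as well, the threshold for the primary claim depends on how many other comparisons happen to be requested. Sample size budgets for neither step.

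**Working it through.** **Inputs from the protocol.** 26 per arm; power 0.80; one-tailed alpha 0.05; d = 0.20 (Sample size). Three visits, interaction first, then simple effects (Data analyses). BSL-23 test-retest r = .73 (Primary outcome measure).

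**Assumptions, not in the protocol.** Equal correlation ρ between any two visits, at 0.3, 0.5 and 0.73. A 12-month effect that persists, halves or vanishes. Family sizes k = 3 (one between-arm comparison per visit), 9 (those plus three visit pairs in each of two arms) or 15 (all pairs of six cells, 6 × 5 / 2).

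**1. The plan's own figure.** n per arm = 2(1.645 + 0.842)² / d². At d = 0.20 this gives 310, not 26. With 26 per arm, power at d = 0.20 is about 18% one-sided. Back-solving 26 per arm for 80% one-sided power (noncentral t) gives d = 0.699, which implies an SD of 8.6 / 0.70 = 12.3. The printed d implies 8.6 / 0.20 = 43. I use d ≈ 0.70 below because it is the value at which the planned 80% exists.

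**2. Sidedness and Bonferroni, no gate** (noncentral t, 26 per arm, d = 0.699, alpha 0.05/k):

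| k | one-sided | two-sided |
|---|---|---|
| 1 | 80.0% | 69.6% |
| 3 | 63.1% | 52.2% |
| 9 | 46.0% | 36.4% |
| 15 | 38.8% | 30.1% |

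Moving from one- to two-sided costs 80.0 − 69.6 = 10.4 points before any correction.

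**3. The interaction gate.** The three arm differences were simulated as normal with variance 2/n and correlation ρ (400,000 draws). The gate is a 2-df Wald statistic above 5.991 on the two changes from baseline. The second step is the post-treatment difference, z = difference / √(2/n). Ranges cover the three 12-month scenarios.

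| ρ | gate passed | gate + uncorrected, two-sided | gate + uncorrected, one-sided | gate + k = 3, two-sided |
|---|---|---|---|---|
| 0.3 | 46–59% | 40.6–51.5% | 43.2–55.1% | 35.0–43.5% |
| 0.5 | 61–74% | 50.0–59.9% | 54.6–66.0% | 41.2–48.5% |
| 0.73 | 88–95% | 65.2–69.4% | 73.2–78.5% | 51.2–54.0% |

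Every cell in the last three columns is below 80%, including those with no Bonferroni correction and the one-tailed test retained.

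**4. The proposed contrast.** The between-arm difference in change has z = d√(n/2) / √(2(1 − ρ)), where d√(n/2) = 0.699 × √13 = 2.52.

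- ρ = 0.3: 2.52 / √1.40 = 2.13; power 57% two-sided, 69% one-sided.
- ρ = 0.5: 2.52 / √1.00 = 2.52; power 71% two-sided, 81% one-sided.
- ρ = 0.73: 2.52 / √0.54 = 3.43; power 93% two-sided, 96% one-sided.

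These use the normal approximation; the t distribution lowers the two-sided figures by one or two points. Steps 3 and 4 are not strictly like for like, because step 3 ends in a cross-sectional difference and step 4 uses change. Part of the gain at high ρ comes from using baseline rather than from dropping the gate.

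**The case against.** The strongest reply is that the protocol never says the primary contrast is Bonferroni-corrected. With two arms, the simple effect of treatment at one visit is a single comparison. The correction may be meant for the pairwise comparisons among three time points, and defining the family is ordinary analysis-plan detail. The interaction could itself be read as the primary test, since it addresses differential change. This stands in part: Bonferroni coverage is a reading, and the undefined family alone would not be a finding. It does not remove the point, because the interaction-first sequence is stated text and reduces power on its own. A 2-df test over three visits is also not the post-treatment question in Study aims.

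A reader might infer that Bonferroni takes the trial from 80% to 35–54%. The documents do not support that. The range combines two-sided testing, the gate and an assumed three comparisons, at an effect size that is not printed. Without the gate, the planned one-tailed test over three comparisons has 63% power. If all 72 were analysed (36 per arm, d = 0.70), it would have 79% one-sided and 70% two-sided.

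It is also fair that d ≈ 0.70 is not the only reconstruction. A total of 52 also arises from a repeated-measures interaction with f = 0.20, two measurements and correlation 0.5 (81% power). The text describes no such calculation. If that was the basis, it was again a single 1-df test of change, with neither gate nor correction.

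Finally, the primary time point is not settled throughout: Sample size opens with 12 months, and Background hypothesises an advantage at both times. Whichever visit is chosen, the route in Data analyses is the same.

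**Conclusion.** The point holds as a mismatch between the stated analysis sequence and the test that was sized. At d ≈ 0.70, 26 analysed per arm and ρ from 0.3 to 0.73, power to declare a post-treatment difference is about 40–69% two-sided (43–79% one-sided) with the gate alone. It is about 35–54% two-sided if Bonferroni over three visits is added. The lower range is conditional on a reading of the Bonferroni sentence and should be labelled so. All these figures rest on the back-solved effect. At the printed d = 0.20 there is no 80% to lose, and that error needs its own correction.

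**What to change.** In Data analyses, name the between-arm contrast in BSL-23 change from baseline to post-treatment, estimated from the GEE model, as the single primary test. Test it at full alpha, whatever the interaction shows and outside the Bonferroni family, with sidedness stated and the same as in Sample size. Keep Bonferroni for the other visit-wise and within-arm comparisons, labelled secondary.

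In Sample size, align the 12-month wording with Study aims and restate power for this contrast over a range of correlations. Under the assumptions above it is about 57%, 71% and 93% two-sided at ρ = 0.3, 0.5 and 0.73. The change therefore does not by itself secure 80% at the lower correlations.

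The cost is one or two sentences in Data analyses and a redone calculation. Type I error for the primary claim stays at 5%, because it is one pre-specified test.
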